## Abstract

**Background:**

Children with epilepsy have significant social impairments, yet evidence-based interventions to address these social difficulties are lacking. Emerging research has shown that social difficulties in children with epilepsy relate to underlying impairments in Theory of Mind (ToM). This paper outlines the protocol for a pilot study that will evaluate the feasibility, acceptability, and efficacy of a novel cognitive behavioural intervention with ToM training for children with epilepsy.

**Methods:**

The intervention will be evaluated in a single-arm case series feasibility study. Ten to 12 children with common forms of epilepsy (8 to 12 years old) will be recruited to participate in 4 small group workshops, held over 4 consecutive weeks. Parents will attend a brief review at the end of each session with their child. Children will complete 4 one-to-one assessments with an investigator assessing ToM and social competence: twice at baseline (4 weeks and 1 day before the intervention), at post-intervention (last day of the intervention) and at follow-up (4 weeks post intervention). Parents will complete online questionnaires at these same 4 time points assessing ToM and social competence of their child. Parents and children will both complete a weekly measure of social competence from baseline 1 to follow-up. Following completion of the intervention, parents will complete two standardised questionnaires assessing treatment acceptability and barriers and facilitators to attendance; children will complete a single questionnaire on treatment acceptability. Information about feasibility outcomes (i.e. recruitment and retention, processing time, suitability of tasks) will be gathered by investigators during the trial. Together, outcomes will be used to refine research methods and make a decision about whether the intervention should be evaluated in a larger scale trial.

**Discussion:**

To our knowledge, this is the first psychosocial intervention to address social competence problems in children with epilepsy. Findings will provide information about a potentially effective treatment that could improve longer term social outcomes for this group.

**Trial registration:**

Australia and New Zealand Clinical Trials Register (ANZCTR): ACTRN12618000974202, registered June 8 2018.

**Electronic supplementary material:**

The online version of this article (10.1186/s40814-019-0393-x) contains supplementary material, which is available to authorized users.

## Background

Epilepsy is a common neurological condition in childhood that is associated with significant psychosocial difficulties: reduced social competence, social isolation and high levels of psychological distress [1, 2]. At present, there are no effective, evidence-based interventions to treat social difficulties in children with epilepsy. This is concerning as social difficulties that emerge in childhood tend to persist in adults with epilepsy and have a negative impact on patients’ social and psychological adjustment and quality of life [3, 4]. Early intervention may reduce the social and emotional burden of epilepsy; however, researchers have struggled to develop effective psychosocial treatments, in part due to limited understanding of the neurocognitive underpinnings of social difficulties in this group. Promisingly, emerging evidence from empirical studies has shown that children with common forms of epilepsy, including genetic generalised epilepsy (GGE) and temporal lobe epilepsy (TLE) have significant impairments in Theory of Mind (ToM), which are related to social competence and social communication problems [5–7]. This has led to suggestion that training children’s ToM may be an effective way of improving social outcomes in this group [8, 9].

Theory of Mind (ToM) refers to the ability to understand the thoughts, intentions, beliefs and emotions of others and oneself [10]. ToM is comprised of component skills including the capacity to understand mental states, including beliefs and knowledge (cognitive ToM), and to identify and communicate emotions (affective ToM) [10]. Interventions targeting ToM have been developed and trialled for children with other neurodevelopmental conditions, including autism spectrum disorder (ASD) and hearing impairment [11–13]. For these groups, ToM interventions have been broadly effective at improving ToM [14, 15], with a recent meta-analysis finding medium-size improvements in children’s ToM following training (Hedges’ *g* = 0.747) [14]. Improvements in everyday social competence following ToM training have been documented in some studies [16, 17] but not others [11, 12]. The efficacy of prior interventions was found to depend on whether the components included in training were appropriate for age and ability level of the target group [14]. This included the suitability of ToM modules (i.e. targeting cognitive and/or affective ToM) and whether strategies were included to assist with the acquisition and/or generalisation of ToM skills (i.e. language exercises, executive functioning [EF] strategies and cognitive behavioural therapy [CBT] skills).

Interventions targeting early developing cognitive ToM (i.e. false belief understanding), which matures between 3 to 5 years, were found to produce large improvements in ToM in pre-schoolers [18, 19] but had little effect on ToM in children over 8 years old [20]. For this age group (≥ 8 years old), interventions that targeted advanced cognitive and/or affective ToM, which emerge between 8 to 12 years old, were successful at achieving improvements in ToM [21]. This is unsurprising, as older children are unlikely to benefit from training in skills that they have already acquired at an earlier developmental age. In addition, several studies included strategies to target cognitive skills that develop alongside ToM, such as language [16, 21] and EF [17, 20]. Including these strategies was found to be beneficial for children with impaired language and EF (e.g. children with ASD) who showed improvements in ToM when these components were included, but not when they were omitted from training [11, 20]. Finally, a few studies included CBT skills alongside ToM training and these studies also reported improvements in children’s everyday social competence [16, 17]. This is consistent with research suggesting that understanding the relationship between thoughts, feelings and behaviours is critical for applying ToM reasoning to the social world [22]. Finally, contextual factors relating to the structure, timing and frequency of sessions have also been found to impact treatment outcomes. Interventions with longer individual sessions and shorter overall training periods were associated with larger improvements in ToM in a recent meta-analytic review [14]. Additionally, involvement of same-age peers, small group sessions, active involvement of group facilitators and inclusion of parent-review sessions have been found to enhance engagement and learning among children in prior interventions targeting ToM and broader social skills [14, 23].

It is unclear whether interventions developed for other clinical groups would be appropriate and/or beneficial for children with epilepsy. This is because children with epilepsy have a unique cognitive and behavioural profile, including impairments in general language abilities and EF that often occur in the absence of impaired intellectual quotient (IQ) [24, 25] and impairments in social competence, social communication and social cognition in the absence of additional features of ASD (e.g. autistic styles of communication and behaviour, such as idiosyncratic language) [26]. Given that the success of prior ToM interventions has depended upon the suitability of treatment components for the target group, strategies required for children with epilepsy may differ from other clinical groups. Thus, we sought to develop a tailored intervention specifically for children with epilepsy, aged 8 to 12 years old. We selected this age range in middle childhood as it is a time of rapid growth in ToM when social and emotional difficulties in patients with epilepsy often emerge [8]. We developed the intervention in accordance with the Medical Research Council (MRC) guidelines for intervention development [27] to address shortfalls of prior ToM interventions in a number of ways. First, the intervention targets advanced cognitive and affective ToM, which have been found to be impaired in children with epilepsy who are between 8 to 12 years old [5–7]. Second, the intervention includes strategies to assist with language and EF, which are commonly impaired in young epilepsy patients [25, 28, 29]. We have included both mental-state [21] and emotion vocabulary [16] language activities, similar to those included in prior ToM interventions targeting the same age group, as research suggests that these are important for developing cognitive and affective ToM, respectively [14]. Third, the intervention includes basic CBT skills alongside ToM training, as this is regarded as important for translating ToM reasoning into observable social behaviours [22]. Finally, we have included various contextual factors that have been associated with better engagement and larger improvements in ToM and social skills (e.g. involvement of parents and same-age peers, small group sessions) [14, 23].

To our knowledge, this is the first intervention that has been designed and trialled specifically for children with epilepsy to target ToM and social impairments. Given the preliminary nature of the intervention, pilot testing is crucial to ensure that it is feasible, acceptable and safe prior to implementation in a larger scale trial. The protocol has been developed and is described in accordance with the Standard Protocol Items: Recommendations for Interventional Trials (SPIRIT) guidelines (see Additional file 1) [30]. The intervention is described according to the Template for Intervention Description and Replication (TIDieR) checklist (see Additional file 2) [31].

### Objectives

The primary objectives of the study are to assess feasibility and acceptability of the intervention for children with epilepsy (8 to 12 years old) with respect to the following factors:Recruitment and retention rates (including attendance at sessions).Processing time for intervention modules.Suitability of tasks (including ability and willingness of children to participate in activities), as determined by observations made by investigators during sessions.Overall acceptability of the intervention as a comprehensive programme, as determined by responses from parents and children on standardised questionnaires.Barriers and facilitators to attending the programme, as indicated by parents of children who participate on a standardised questionnaire.

The secondary objective is to determine whether the intervention is effective at improving

(1) ToM and (2) social competence, as determined by children’s performance on behavioural tasks as well as responses from children and parents on standardised questionnaires.

### Trial design

Pilot and feasibility study guidelines were consulted in designing and planning the study [32, 33]. The study will employ a double baseline case series design, and the intervention will be run as a single-arm open-label pilot. The framework for the study is exploratory. The decision to conduct an open-label pilot was guided by research by Leon and Davis [33], who state that open-label studies in which participants are recruited to known albeit experimental interventions with no risk of receiving placebo are best practise in pilot trials. A case series was selected over a single-case or larger scale randomised controlled trial (RCT) for feasibility, ethical and methodological reasons. Case series are increasingly used in cognitive neuropsychology and are considered more robust and generalisable than single-case designs [34, 35]. Case series involve recruiting a small sample of children to a single experimental condition and assessing individual change in performance across the course of treatment [35]. The most robust and validated method for assessing within-subject change in case series is visual analysis, a method that requires each participant to be assessed at least twice prior to starting treatment (i.e. double baseline). A double baseline approach will be achieved in the current trial by assessing children twice before treatment begins (i.e. baseline 1 and 2). This will provide a stable measure of performance before the intervention, which can be compared to performance on the same measures at post-intervention and follow-up. This approach is common in case series interventions and allows researchers to conclude with some certainty that improvements are attributable to a given treatment and not to practice effects or the passage of time [35]. A double baseline design is also required for the approach that we will use to evaluate outcomes (i.e. visual analysis, see the “Statistical methods” section for more details about this method). A larger scale RCT was not considered appropriate for the current study as this is the first time the intervention will be trialled, and it does not have known positive effects.

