
#### Secondary outcome measures

##### Theory of Mind (ToM)

The strange stories task [47] will be used as the primary measure of change in ToM. Parallel versions of the task will be administered to children at baseline 1, baseline 2, post-intervention and follow-up. The strange stories task contains 12 social stories in which there is a discrepancy in characters’ perspectives or beliefs and children must explain the discrepancy with reference to characters’ thoughts and feelings. Responses are scored on a 3-point Likert scale (0 = no reference to thoughts and feelings, 1 = reference to thoughts or feelings, 2 = reference to thoughts and feelings). A single total ToM score is generated by summing items (range = 0 to 24). Three control stories from the strange stories task that are comparable in length and difficulty, but contain no reference to thoughts or feelings of characters, will also be administered to obtain a measure of general story comprehension (range = 0 to 6). The strange stories task was selected as empirical studies have found that children with GGE and TLE have significant impairments on this task [6, 7]. An additional (secondary) measure of change in ToM will be obtained with the Theory of Mind Inventory (TOMI) [48], which will be completed by parents at the same 4 time points. The TOMI is a 42-item parent-report questionnaire that assesses ToM in children aged 3 to 17 years old. Parents rate how accurate statements are for their child on a 5-point Likert scale (1 = definitely not true to 5 = definitely true), and scores are summed to generate a total raw score (range = 42 to 220), which is converted into a percentage total score (range = 0 to 100). The TOMI is being included as it has been found to be sensitive to change following interventions in other clinical populations [48].

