#### Procedure for intervention delivery and assessments

Children will participate in 4 small group workshops held over 4 consecutive weeks at the Psychology Clinic at The University of Sydney. Each workshop will last for approximately 2 to 3 h and will be divided into 2 to 3 sessions (20 to 50-min each), each separated by a 10- to 15-min break. The final 15- to 30-min of each session will be a review with parents and children.

Children will complete 4 one-to-one assessments with an investigator at baseline 1 (4 weeks before the intervention begins), baseline 2 (1 day before the intervention begins), post-intervention (last day of intervention) and follow-up (4 weeks after the intervention). During assessments, children will complete a behavioural task assessing ToM and parents/guardians will complete questionnaires that assess ToM and social competence of their child. A brief weekly measure of social competence will be completed by both parents and children from baseline 1 to follow-up. Assessments with children will be conducted individually, face to face, at The University of Sydney Psychology Clinic or participants homes. Parent questionnaires and weekly measures will be completed online.

Following completion of the intervention, parents and children will attend face-to-face debriefing interviews to discuss the child’s participation and provide feedback. Parents will complete two online questionnaires assessing treatment acceptability and barriers and facilitators to attending the programme. Children will complete a single questionnaire assessing treatment acceptability that parallels the questionnaire completed by parents. These questionnaires will be completed before the debriefing interview to minimise bias in responding based on clinician feedback.

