### Statistical methods

Primary analyses will report results relating to feasibility outcomes, which do not rely on quantitative statistical tests. Secondary analyses will involve data pertaining to children’s performance on tasks of ToM and social competence. Individual participant scores on secondary outcome measures will be plotted graphically and visual analysis will be used to assess change in performance from baseline 1 to follow-up. Visual analysis involves inspecting performance during an intervention and at follow-up and comparing this to a baseline mean (i.e. average of scores at baselines 1 and 2) [60]. Although new quantitative methods have been devised to estimate effect sizes in case studies, the use of these measures has been advised against in pilot studies due to the potential for inaccurate interpretation of results with unpowered samples [61]. Thus, visual analysis along with inspection of simple, descriptive statistics was considered the most appropriate method for the current study. Both primary and secondary analyses will be used to draw a conclusion about whether the study should be expanded into a larger scale trial. Given the small sample size and lack of quantitative statistical tests, we do not anticipate that statistical methods will be required to handle missing data; however, missing data for individual participants will be reported in papers arising from the research with an explanation of why data was not obtained.

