### Overall success of the intervention

The overall success of the intervention and decision to evaluate it in a larger scale trial will be determined with both primary and secondary outcomes. A final decision about the protocol will be made upon completion of the study [32]:Stop (main study not feasible). None of the primary feasibility outcomes are met *and* a negative trend is observed in secondary outcomes *or* other adverse effects are reported.Continue but modify protocol (feasible with modifications). One or more of the primary feasibility outcome measures are not met.Continue without modifications (feasible as is). All of the primary feasibility outcomes are met *and* a positive trend is observed on both secondary outcomes (ToM and social competence).

Trends on secondary outcomes will be determined with visual analysis, as described in the “Statistical methods” section. A negative trend would be indicated by scores that fall below the baseline mean and positive trends by scores that fall above the baseline mean [60]. Scores that are comparable to baseline or fluctuate around the baseline mean would indicate neither a positive nor negative trend. A negative trend for ≥ 50% of participants would be sufficient to stop the main study (decision a). A positive trend on ≥ 50% of participants will be considered sufficient to continue the study, with or without modifications (decisions b or c). Smith [60] provides further details about this method. Participants included in the pilot study will not be included in an ongoing trial that results from this research to reduce the potential for bias in results.

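### The trend rule compares later scores only with the mean of the two baselines, so it cannot support the claim that gains are not due to practice or time

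*Protocol article*

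**What the plan says.** All references are to the protocol article. Under Trial design: "The study will employ a double baseline case series design, and the intervention will be run as a single-arm open-label pilot". The same section says that assessing children twice before treatment gives a stable pre-treatment measure, and that this allows researchers to "conclude with some certainty that improvements are attributable to a given treatment and not to practice effects or the passage of time".

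Under Statistical methods, each child's scores are plotted and inspected visually, "comparing this to a baseline mean (i.e. average of scores at baselines 1 and 2". Under Overall success of the intervention: "A negative trend would be indicated by scores that fall below the baseline mean and positive trends by scores that fall above the baseline mean". Scores close to the baseline mean, or moving around it, count as neither, but no width is given. At group level: "A positive trend on ≥ 50% of participants will be considered sufficient to continue the study, with or without modifications". Continuing without modifications also requires every primary feasibility outcome to be met and a positive trend on both ToM and social competence.

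The four assessments are listed as "baseline 1 (4 weeks before the intervention begins), baseline 2 (1 day before the intervention begins), post-intervention (last day of intervention) and follow-up"; the last of these takes place four weeks after treatment ends. The strange stories task has parallel versions across the four assessments, and "Three control stories from the strange stories task that are comparable in length and difficulty" are also given. No parallel versions over time are mentioned for the TOMI, SPP, SDQ or CBCL. The limitations paragraph in the Discussion admits that there is no control group, but names as consequences only the missing power calculation and the inability to study randomisation.

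**The concern.** In a single-arm study, the untreated interval between baselines 1 and 2 is the main evidence on how much a score rises through repetition or growing up alone. Averaging the two baselines takes that evidence out of the rule. A child whose scores climb steadily from the first test onwards, with no benefit from the workshops, ends above the baseline mean and is classed as a positive trend.

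Such a climb is plausible on the protocol's own account: the Background says this age range was chosen partly because ToM develops quickly in these years. Parallel story versions reduce recall of particular items, but not familiarity with the task and not maturation.

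Two things are at stake. Whether the intervention improves ToM and social competence is a stated secondary objective, and readers are assured that practice and time have been excluded as explanations. The trend is also part of the decision to proceed to a larger trial.

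**Working it through.** The protocol states no figure to reproduce here: it gives no alpha, power, SD or expected drift. The check is algebra, then an illustration on stated assumptions.

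**Inputs from the protocol.** Four assessments; comparator = mean of baselines 1 and 2 (B1, B2); positive = above that mean; group threshold 50% or more; 10 to 12 children. B1 is at week −4 and B2 at day −1, about week −0.14. The intervention is described as "Children will participate in 4 small group workshops held over 4 consecutive weeks", so the last workshop is about week 3 and follow-up about week 7.

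**Step 1: expected bias with no treatment effect.**

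- *Gain d at each repeat.* Expected scores are B1, B1 + d, B1 + 2d and B1 + 3d. The baseline mean is B1 + 0.5d. Excess at post-intervention: 2d − 0.5d = 1.5d. At follow-up: 3d − 0.5d = 2.5d.
- *One-off gain d after the first test.* Later scores are all B1 + d and the baseline mean is B1 + 0.5d. Excess: 0.5d at both later assessments.
- *Linear growth b per week.* The baseline mean is centred at (−4 − 0.14)/2 ≈ −2.07 weeks. Excess: (3 + 2.07)b ≈ 5.1b at post-intervention and (7 + 2.07)b ≈ 9.1b at follow-up.

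In every case drift enters the comparison with the same sign as benefit.

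**Step 2: chance of meeting the group threshold with no treatment effect.** Assumptions: independent normal errors with SD 1, and any excess over the mean counts because the protocol gives no width for scores close to baseline. The difference between the post-intervention score and the baseline mean has variance 1 + 1/2 = 1.5. So the chance that one child is positive at post-intervention is Φ(1.5d/√1.5) for a gain at each repeat and Φ(0.5d/√1.5) for a one-off gain. At d = 0.25 these are Φ(0.306) = 0.620 and Φ(0.102) = 0.541. At d = 0.5 they are Φ(0.612) = 0.730 and Φ(0.204) = 0.581. The binomial chance of at least 5 positives among 10 follows. The last column requires both post-intervention and follow-up to exceed the mean and comes from simulation, with per-child chances of 0.304, 0.477 and 0.647.

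| Drift d (error SDs) | Gain at each repeat, post only | One-off gain, post only | Gain at each repeat, post and follow-up |
|---|---|---|---|
| 0 | 62% | 62% | 16% |
| 0.25 | 87% | 72% | 57% |
| 0.5 | 97% | 80% | 90% |

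With 12 children and a threshold of 6, the first column becomes 61%, 88% and 98%.

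**Step 3: what belongs to drift.** The 62% at d = 0 is produced by the 50% threshold, not by practice. The part due to drift is the rise above it: 87 − 62 = 25 points at 0.25 SD for a gain at each repeat, and 72 − 62 = 10 points for a one-off gain. If both later scores must exceed the mean, the rise at 0.25 SD is 57 − 16 = 41 points.

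**The case against.** The strongest reply is that the protocol is modest. The framework is called exploratory, the attribution is hedged, and ToM and social competence are secondary. An unmodified continuation also needs every feasibility outcome to be met, and continuing leads to another trial, not to an efficacy claim. This stands as a reason for restraint about severity. It does not repair the sentence, because the stated rule does nothing to exclude practice or time.

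A reader might infer that the change between baselines is thrown away altogether. The protocol does not support that. Both baselines appear on each child's plot, and the SPP is rated weekly from baseline 1, so a pre-treatment slope can be seen. The narrower point remains: the rule that classifies a trend refers only to the mean.

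A reader might also add regression to the mean. The protocol gives no basis for it: the eligibility criteria contain no cut-off on ToM or social scores, and recruitment takes the first eligible children in the database.

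Finally, the illustration depends on assumed drift and on its shape. Parallel versions and diminishing practice would favour the smaller, one-off figures for the strange stories task. The four-assessment practice model does not describe the weekly SPP.

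**Conclusion.** The concern holds. The attribution claim under Trial design is stronger than the rule under Statistical methods and Overall success of the intervention can support, and the limitations paragraph does not say so. With no treatment effect, a gain of d per repeat appears as 1.5d at post-intervention and 2.5d at follow-up; a one-off gain still leaves 0.5d. The algebra needs no distributional assumption. The probabilities in the table rest on assumed values of d, independent errors of SD 1 and no band for scores close to baseline, so they show direction and range, not a forecast. It would go too far to say that drift alone accounts for 87% or 97%, because 62% arises with no drift when only the post-intervention score is used. The feasibility outcomes are untouched. This should be fixed, mainly in the wording and reporting.

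**What to change.** 1. Under Trial design, delete the attribution sentence or weaken it to say that two baselines help to show whether scores were already changing before treatment.
2. In the limitations paragraph, state that without a control group, practice, maturation and the passage of time cannot be separated from treatment.
3. Under Statistical methods, report for each child the B1-to-B2 change beside the B2-to-post-intervention and B2-to-follow-up changes, and the weekly pre-treatment slope for the SPP. Say that a positive trend will not be read as evidence of a treatment effect where a similar rise is already present between the baselines.
4. Show the control-story scores descriptively beside the ToM scores, each as a proportion of its maximum, since the raw ranges (0 to 6 and 0 to 24) are not comparable.

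A tempting alternative is to call the result positive only if more children improve from B2 to post-intervention than from B1 to B2. It should not become a decision rule. In simulation with 10 children and the same error assumptions, it is met about 42% of the time with neither drift nor effect. With an assumed real effect of 0.75 SD, it is met only 53% of the time after a one-off practice gain of 0.5 SD, and 31% after one of 1 SD. Two baseline points per child are too few for a mechanical correction.

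The cost is a few sentences, slightly more reporting and a more modest efficacy statement. No new data are needed.
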